### Treatment

The treatment of patients outside the hospital will be according to the current Dutch national primary care guidelines.^19–21^ In addition to these oral treatment options for bacterial pneumonia (amoxicillin or doxycycline), the treating physician can treat patients in the care pathway with oral moxifloxacin, or intramuscular ceftriaxone in patients with unreliable oral intake or where there is little supervision on the intake, which will be administered by a specialised nurse at home or in the nursing home. Furthermore, the treating physician can treat patients with influenza in the care pathway with baloxavir. Patients who visit the ED but will be treated outside the hospital will receive their first dose of antibiotics intravenously at the ED. The treatment of the control group will be according to local hospital guidelines, which are based on the Dutch national guidelines for bacterial pneumonia (amoxicillin (intravenously or oral) or ceftriaxone (intravenously) for moderate-to-severe pneumonia), COVID-19 and influenza.^22–24^ In the care pathway, patients can receive oxygen suppletion with a maximum of 5 liters at home or in the nursing home.

### Monitoring

Patients in the hospital-at-home group will be visited by a specialised nurse within 4 hours after registration. During this visit, the nurse will bring a monitoring kit (pulsoximeter and thermometer) and a printed registration form and will instruct the patient (and his/her informal caregiver) about their use: the patient, informal caregiver and/or nurse will write the vital parameters of the patient down on the registration form at least three times a day. The GP will contact the patient at least once a day to discuss his/her condition and vital parameters together with whether the patient went out of bed that day and whether the patient has fallen. In case of doubt, the GP will visit the patient. Based on these consultations, the GP will monitor the patient, reduce oxygen suppletion if applicable and decide when the monitoring stops. To guarantee a 24/7 safety net, the GP will inform the general practice centre about the patient being treated at home according to the care pathway.

In the nursing home group, monitoring will be similar. Nurses will monitor the vital parameters of the patient at least three times a day and discuss them with the elderly care physician, who will reduce oxygen suppletion if applicable and will decide when the monitoring stops and the patient is fit enough to leave the nursing home. The monitoring of patients in the control group will be according to local hospital standards.

### Outcomes

The primary outcome is the feasibility of the care pathway, which is defined as the percentage of patients treated outside the hospital, according to the care pathway, whom fully complete their treatment without the need for hospitalisation within 30 days of follow-up. This will be measured by the amount of hospitalisations within 30 days of follow-up in patients treated outside the hospital.

The secondary outcomes are the safety of the care pathway (30-day mortality and occurrence of complications (readmissions, delirium, falls) within 30 days); satisfaction, usability and acceptance of the care pathway (30-day satisfaction questionnaires (patients, informal caregivers and treating physicians) and semi-structured in-depth interviews with the first 10 patients and their informal caregivers in the hospital-at-home group (and the treating GPs), nursing home group and control group after 2–3 weeks); total number of days of bedridden status or hospitalisation; sleep quantity in the first 2 days after inclusion and on the 7th day as assessed by the core Consensus Sleep Diary; sleep quality, functional outcomes and QoL.^25^ Sleep quality will be assessed by the Patient-Reported Outcomes Measurement Information System (PROMIS) Sleep Disturbance short form 8b on day 7 and day 30 after inclusion.^26 27^ Functional outcomes will be measured using KATZ-15 at 30 days, 6 and 12 months.^28–30^ QoL will be assessed using EQ-5D-5L at 30 days, 6 and 12 months.^31 32^ If available, Dutch validated questionnaires are used.

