### Eligibility criteria

To be eligible to participate, a patient must meet all the following criteria: age≥65 years, clinical diagnosis of an acute moderate-to-severe (Pneumonia Severity Index (PSI) class≥3 or Confusion, Urea, Respiratory rate, Blood pressure and age≥65 years (CURB-65) score≥2) LRTI or pneumonia, an oxygen saturation≥92% and a respiratory rate≤24 breaths/minute with a maximum of 5 liters of oxygen (or adjusted oxygen saturation cut-offs as clinically indicated (eg, for patients with chronic obstructive pulmonary disease) by the physician) and written informed consent (IC) for participation.^16 17^ Exclusion criteria are: chemotherapy for solid organ malignancy (<2 months before presentation), active haematologic malignancy, immunocompromised status (eg, solid organ transplants) and/or severe dementia (Clinical Dementia Rating Scale Sum Of Boxes score 16–18).^18^ To be eligible to participate, an informal caregiver must meet all the following criteria: age≥18 years, being an informal caregiver of a patient included in the study and written IC for participation. To be eligible to participate, a treating physician must meet all the following criteria: physician of a patient included in the study at the main location of treatment, the physician should have treated the patient for at least≥2 (consecutive) days and written IC for participation.

Due to logistical limitations (absence of own GPs and evening/night/weekend shifts in nursing homes), the care pathway will be active on weekdays (Monday–Friday) between 08.00 and 18.00 hours for the hospital-at-home treatment and every day (Monday–Sunday) between 08.00 and 20.00 hours for the admission on a recovery bed in a nursing home. Patients who present at their GP and/or at the ED with an acute LRTI or pneumonia when the care pathway is active will be eligible to be treated according to the care pathway. Patients with an acute LRTI or pneumonia who are hospitalised subsequently to this ED presentation will receive the local standard of hospital care and will therefore not be included.

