#### Control group

Patients who fulfil the inclusion criteria and do not meet the exclusion criteria of the care pathway, and are hospitalised on weekdays outside office hours (18:00–08:00 hours) or weekend days due to inactivity of the care pathway, will serve as a control group.

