### Sample size

Ideally, 50 patients will be treated outside the hospital (care pathway group) and 50 patients will be treated in the hospital (control group). A power analysis was performed for the evaluation of the feasibility of the care pathway. In clinical practice, approximately 10% of the hospitalised patients are readmitted to the hospital after discharge. Our hypothesis is that in at least 75% of the older adults with an acute LRTI or pneumonia who are treated outside the hospital (at home or in a nursing home) according to the care pathway (care pathway group), hospitalisation can be avoided (complete treatment outside the hospital during 30-day follow-up). An 80% power with an alpha of 0.05 for an one-sample study will be achieved if 40 patients are recruited for the care pathway group.

For the qualitative endpoints, data collection (interviews) will be performed until data saturation is reached. When a patient is included and his/her informal caregiver and/or treating physician does not want to participate or cannot participate in the study, the patient will remain in the study and no extra patient will be included to make up for the missing informal caregiver and/or physician.

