### Data analysis plan

The primary outcome is the feasibility of the care pathway. This will be quantitative data. Categorical variables will be presented as counts and frequencies. The quantitative data will be analysed with the Statistical Package for the Social Sciences (SPSS) V.28.

The secondary outcomes will be established by comparing the patients in the care pathway group with the patients in the control group during follow-up. Secondary outcomes are the safety of the care pathway (30-day mortality and occurrence of complications within 30 days); the satisfaction, usability and acceptance of the care pathway; the total number of days of bedridden status or hospitalisation; sleep quantity and quality; functional outcomes and QoL.

Categorical variables will be presented as counts and frequencies. Differences between groups will be tested with χ^2^ tests and multivariate logistic regression models. Continuous data will be presented as means (standard deviations) for normally distributed data or medians (interquartile ranges) for non-normally distributed data. Differences between groups will be tested with independent t-tests or one-way Analysis Of Variance (ANOVA) tests (normal distribution), or Mann-Whitney U or Kruskal-Wallis tests (no normal distribution) depending on the amount of groups to be compared per analysis, and by multivariate linear regression models. All tests of significance will be at two-tailed 0.05 level. The 95% confidence intervals will be used to assess the presence/absence of associations. The quantitative data will be analysed with SPSS V.28.

All recorded interviews will be transcribed by two research team members and hereafter then coded with Atlas.ti V.22. The interview recordings will be saved in a secured folder on the network of the coordinating hospital and will be deleted after verbatim transcription. Transcriptions will be saved on the network of the coordinating hospital. We will apply thematic content analysis to identify and categorise recurrent themes/elements in the interviews. Thereby, we aim to classify the qualitative data in the right sections (implementation, methods, context) of the process evaluation of the implementation of the care pathway.

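### Bedridden-or-hospital days are tested between groups defined by hospital admission, so the hospital-day part differs by definition; readmission has no common meaning across the groups

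*Protocol article*

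**What the plan says.** The Outcomes section names "total number of days of bedridden status or hospitalisation" as one secondary outcome. It defines safety as "30-day mortality and occurrence of complications (readmissions, delirium, falls) within 30 days". The Data analysis plan states: "The secondary outcomes will be established by comparing the patients in the care pathway group with the patients in the control group during follow-up". It provides t-tests or rank tests for continuous outcomes, χ² tests for categorical ones and regression models, all at a two-sided 0.05 level.

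The groups are fixed in two places. Under Control group, eligible patients who are "hospitalised on weekdays outside office hours (18:00–08:00 hours) or weekend days due to inactivity of the care pathway, will serve as a control group". Under Eligibility criteria, patients who come to the emergency department in pathway hours and are "hospitalised subsequently to this ED presentation will receive the local standard of hospital care and will therefore not be included".

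On measurement, the Monitoring section has the GP ask home patients each day whether they got out of bed, and calls nursing-home monitoring similar. For controls: "The monitoring of patients in the control group will be according to local hospital standards". Under Monitoring data, information on illness duration and complications for controls comes from hospital records; out-of-bed status is not named. Table 3 has no row for it.

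**The concern.** At inclusion, 100% of controls and 0% of pathway patients are in hospital, because that is how the groups are formed. An outcome that counts hospital days then scores the grouping rule as well as the illness. Read as written, a day in hospital counts whether or not the patient is up, while a day at home or in a nursing home counts only if the patient is bedridden. Two identical patients with the same course would score differently. Regression on baseline variables cannot remove a difference that the scoring rule creates.

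The readmission item in "occurrence of complications (readmissions, delirium, falls) within 30 days" has a different fault. A pathway patient has no index stay to be readmitted from, so the same word covers two events, and the groups are at risk for different lengths of time. The days result could be reported as benefit, and the admissions result as safety or harm, when neither contrast compares like with like.

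**Working it through.** **Inputs from the article.** Planned size 50 per group; about 10% of hospitalised patients readmitted after discharge (no time window given); hospitalisation avoided in at least 75% of pathway patients, so up to 25% admitted; two-sided 0.05.

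**Assumed, because the article gives no figure.** Mean stay L = 3, 5 or 7 days; the same mean illness duration outside hospital; share f of those illness days spent in bed, 0 to 100%; pathway admissions p = 10% or 25%; the index stay counts in the controls' total.

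**The plan's own figure.** The Sample size section gives 40 patients for 80% power. Taking 90% as the reference (100% − 10%, an inference) against 75%:

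n = [(1.96·√(0.9·0.1) + 0.842·√(0.75·0.25)) / 0.15]² = 40.3.

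This reproduces 40 (power at 40 is 79.8%). On this reading, the plan already sets readmissions after discharge against first admissions from the pathway.

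**Days composite with no effect on illness.** Controls expect L + 0.10·L = 1.1L days. Pathway patients expect f·L bedridden days plus p·L hospital days. The difference is

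D = (1.1 − p − f)·L.

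- Hospital days alone (f = 0): D = 3.0, 5.0, 7.0 days at p = 10%; about 2.6, 4.3, 6.0 days at p = 25%.
- D is zero at f = 1.1 − p, that is 100% at p = 10% and 85% at p = 25%. Beyond 85% in the second case the sign reverses.

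Probability of p < 0.05 in simulation (50 v 50, Mann-Whitney, 500 runs per cell; stays and illness days drawn as 1 + Poisson(L − 1)), for L = 3 / 5 / 7:

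| f | p = 10% | p = 25% |
|---|---|---|
| 0% | 1.00 / 1.00 / 1.00 | 1.00 / 1.00 / 1.00 |
| 25% | 1.00 / 1.00 / 1.00 | 1.00 / 1.00 / 1.00 |
| 50% | 1.00 / 1.00 / 1.00 | 0.92 / 0.96 / 0.98 |
| 75% | 0.63 / 0.76 / 0.87 | 0.18 / 0.26 / 0.32 |
| 100% | 0.04 / 0.04 / 0.04 | 0.18 / 0.17 / 0.21, mean difference reversed |

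**Readmissions on the article's own rates, 50 per group.**

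- First admissions (pathway) against readmissions (control): up to 25% v 10%. With 12 v 5 patients, χ² p = 0.06; power for 25% v 10% is 51%. The pathway looks worse.
- Any admission: 12 of 50 v 50 of 50, Fisher p = 4 × 10⁻¹⁷. The pathway looks better.
- Only admissions that follow an earlier one: if 10% of the 25% return, 2.5% v 10%. The pathway again looks better.

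**Days at risk.** On a 30-day clock from inclusion, a control is at risk for 30 − L days. If 10% is a 30-day post-discharge rate with constant hazard (an assumption), the control rate becomes 1 − 0.9^((30 − L)/30): 9.0%, 8.4% and 7.8% for L = 3, 5, 7. That is about one patient in 50 at most.

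**The case against.** Four points can be made for the plan.

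*Fewer hospital days is what the pathway is for, so counting them is legitimate.* This would stand if all eligible presenters in active hours were compared with all those in inactive hours, wherever they were treated. Here patients admitted through the emergency department in pathway hours are left out, so the zero at inclusion comes from selection.

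*The authors already call the clinical outcomes explorative.* They do, in the Discussion, but because illness tends to be more severe outside office hours. That is confounding; the scoring problem would remain with identical patients in both groups. The stated small sample does not address it either.

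*The outcome includes bedridden days, which pathway patients can accrue at home or in a nursing home.* This stands. A reader might infer that the whole difference is built in, that the test is bound to favour the pathway, or that nursing-home days never count. The article supports none of these: the difference is only partly built in, its size rests on unstated quantities, and bedridden nursing-home days can count. A condensed article may also leave the counting rule to the full protocol.

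*No readmission difference is built in.* This also stands: 10% in each group gives no difference. A reader might infer that pathway readmissions are near zero by definition, but the Sample size and Outcomes sections treat admissions from the pathway as events to be counted. The unequal risk period alone is a small effect.

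**Conclusion.** The point holds in a limited form. The hospital-day component of the composite differs by group definition, so a significant result cannot be read as an effect on illness. The artefact is large if pathway patients are in bed for up to about half of their illness days, uncertain at three quarters, and absent or reversed if they are in bed nearly every day. These statements rest on assumed stays, assumed time in bed and counting the index stay.

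For readmissions the defect is that a first admission is set against a second one over unequal risk periods. On the article's own rates the direction depends on which reading is chosen.

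It would go too far to say that these outcomes tell us nothing. Bedridden days outside hospital remain informative, and the primary outcome, a one-group percentage, is unaffected. The issue concerns secondary outcomes and should be corrected before they are compared.

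**What to change.** 1. Split the composite. Report hospital days per group descriptively, without a between-group test.
2. Compare bedridden days alone, recorded the same way in both groups: a daily out-of-bed yes/no item from the control record as well as from home and nursing-home monitoring.
3. For admissions, name the event in each group: first admission in the pathway group, readmission after discharge in controls. Show all pathway admissions, including those during treatment, and state the days at risk. Do not present the contrast as a like-for-like safety comparison.

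Two tempting alternatives should be avoided. A tested outcome of days at the pre-illness residence repeats the fault, because index hospital days again count against every control and a hospital-at-home patient loses none. Counting pathway admissions only after release from the pathway would remove treatment failures, up to 25% of patients, from the safety comparison.

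The cost is a redefinition of two outcomes, one extra item in the control record, and a days result that will look less favourable to the pathway.

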### Study procedures

#### Patient presenting at GP

When a GP decides to treat a patient at home or in a nursing home according to the care pathway, the GP will perform a physical examination, measure the vital parameters (heart rate, blood pressure, respiratory rate, oxygen saturation and temperature) and will perform the standard diagnostics package (Table 2): nasopharyngeal swab (SARS-CoV-2, influenza and respiratory syncytial virus (RSV)) and the adjusted Acute Presenting Older Patient (APOP) screening.^33^ The GP will inform the patient (or representative (eg, in case of incapacity due to dementia/delirium)) about the study on inclusion in the care pathway and asks for oral IC. When the patient or representative (on behalf of the patient) agrees to participate, the GP will hand over the patient information leaflet (PIL) and inform the research team. Within one workday, a research team member visits the patient (and representative if applicable) at home or in the nursing home to provide written IC and collect data.

**Table 2 T2:** Diagnostics packages at the primary care centre and the emergency department

	Primary care centre	Emergency department
Laboratory tests	Optional	Blood cell count including differentiation C reactive protein Sodium/potassium/glucose Kidney function (creatinine/urea) Optional: D-dimer/NT-proBNP
Microbiology	Nasopharyngeal swab (PCR): SARS-CoV-2 Influenza A/B Respiratory syncytial virus	Nasopharyngeal swab (PCR): SARS-CoV-2 Influenza A/B Respiratory syncytial virus
Radiology	Optional	X-ray and/or CT scan of the thorax
Clinical prediction rules	Adjusted APOP screening	APOP screening PSI or CURB-65 measurement
Electrocardiogram	Optional	Yes

APOP, Acute Presenting Older Patient; CURB-65, Confusion, Urea, Respiratory rate, Blood pressure and age≥65 years; NT-proBNP, N-terminal pro brain natriuretic peptide; PCR, Polymerase Chain Reaction; PSI, Pneumonia Severity Index; SARS-Cov-2, Severe Acute Respiratory Syndrome Coronavirus 2.

When a patient does not want to participate in the study, no research data will be collected and the patient will still be managed according to the care pathway.

#### Patient presenting at the ED

When the GP decides to refer the patient to the ED for additional assessment or a patient presents at the ED, a predefined diagnostics package (Table 2) will be performed including laboratory tests, nasopharyngeal swab (SARS-CoV-2, influenza and RSV), clinical prediction rules (PSI or CURB-65, and APOP), imaging of the chest (X-ray and/or CT scan) and an electrocardiogram. The treating ED physician will inform the patient (and representative if applicable) about the study (including handing over the PIL) on inclusion in the care pathway (hospital-at-home treatment or nursing home admission) or on hospitalisation for patients eligible for the control group, and will ask the patient (or representative if applicable) for oral IC to participate. Within one workday, a research team member visits the patient (and representative if applicable) on location to provide written IC and collect data.

#### Monitoring data

Besides the data from the registration forms of patients in the hospital-at-home group, GPs will collect information regarding illness duration during their treatment/monitoring of the patient, thereby providing insight into the occurrence of complications and the percentage of complete treatments at home. Elderly care physicians will collect similar information in the electronic health records (EHRs) of patients in the nursing home group. For patients in the control group, this information will be extracted from the hospital EHRs.

#### First study visit

A research team member will visit the patient on location (at home, in the nursing home or hospital) on the first workday after the start of the treatment. During this visit, patients (and their representatives if applicable) will be able to ask additional questions about the PIL and the study. If a patient (or representative on behalf of the patient) agrees to participate, written IC will be asked for participation. In case a representative has provided written IC for an incapacitated patient (eg, in case of delirium), and the patient’s medical condition improves over time, the patient will be asked for written IC when the patient is considered competent again. When a patient has given written IC, their informal caregiver and treating physician will also be approached to participate in the study.

During this first visit, baseline information will be collected from the patient. This will include demographic information and a geriatric assessment (GA). A GA is an evidence-based, systematic procedure used to objectively describe the health status of older adults, focusing on somatic, functional and psychosocial domains; and aimed at constructing a multidisciplinary treatment plan. The GA will include the following validated tests: the Charlson Comorbidity Index, G-8 screening tool, 6-item Cognitive Impairment Test, functional status (KATZ-15 and living situation) and QoL (EQ-5D-5L).^34–36^ Ethnicity and religion are included in the demographic information as the area of The Hague has a multicultural society and these factors may influence a patient’s care system and thereby the choice of treatment location. Dementia research has shown that a considerable amount of people with a migration background makes limited use of professional homecare, and needed care is often taken over by family members.^37 38^

During this visit, patients will receive a core Consensus Sleep Diary to fill in on the 2 upcoming days and on the 7th day after inclusion. Patients will also receive a PROMIS Sleep Disturbance short form 8b to fill in on the 7th day after inclusion. The sleep quality/quantity forms will be collected 1 week after inclusion. In the hospital-at-home group, the registration forms will be collected together with the monitoring kits when the patient is released from the care pathway. See Figure 2 and Table 3 for an overview of the time points and collected data.

